## Abstract

**Background:**

An estimated two billion people, over one third of the world’s population, have latent infection with *Mycobacterium tuberculosis* (LTBI). Patient adherence to LTBI treatment is currently poor given that individuals show no symptoms of illness and may not feel that they are at risk of developing active tuberculosis (TB). Short text messages can serve as a simple reminder to take medications and address barriers to adherence such as forgetfulness and lack of social support.

**Methods/design:**

We aim to determine the feasibility and acceptability of text reminders for improving adherence in latent TB patients using a randomized controlled single-blinded trial, measuring adherence through an increase in treatment completion rates. Forty adult LTBI participants will be randomized to either text messages plus phone call reminders or phone call reminders only (usual care). Recruitment, retention, and study acceptability will be assessed as primary outcomes.

**Discussion:**

This pilot study will examine the feasibility of using text messaging for increasing adherence to treatment for latent tuberculosis infection. The study will allow for evaluation of process measures and challenges and development of a model for scaling up an effectiveness trial for increasing treatment adherence.

**Trial registration:**

NCT02690818 (Clinical Trials.gov)

**Electronic supplementary material:**

The online version of this article (doi:10.1186/s40814-017-0128-9) contains supplementary material, which is available to authorized users.

## Background

Tuberculosis (TB) is a leading cause of death from an infectious disease worldwide. An estimated two billion people, one third of the world’s population, are infected with *Mycobacterium tuberculosis*, resulting in approximately 1.4 million deaths annually [1]. People with untreated or undiagnosed TB who do not complete their prescribed treatment regimen pose major health risks to themselves and to the general population. Those patients who do not adhere to treatment for active TB remain infectious longer and are more likely to relapse and die. They are also vulnerable to developing drug-resistant tuberculosis [2].

### Adherence to latent tuberculosis infection therapy

Approximately one third of individuals exposed to someone with active TB disease develop latent TB infection (LTBI) [3]. Patients who develop LTBI are asymptomatic and non-contagious but the overall lifetime risk of LTBI progression to active TB is estimated at approximately 5–10% [4]. This risk is greatly increased among immunosuppressed individuals, including those with HIV, diabetes, and heavy steroid use [5, 6]. The populations with the highest burden of LTBI in the USA are primarily from immigrant, refugee, and non-English speaking communities. Ten million individuals in the USA, including 19% of foreign-born residents, are estimated to have LTBI [7, 8]. One approach to reduce the burden of TB is to detect and treat persons while they still have LTBI to prevent disease development. This approach is recommended for individuals at increased risk for progression to disease [9]. These include persons who were born in countries with increased tuberculosis prevalence and persons who live in high-risk congregate settings. Patient adherence to LTBI therapy is low as LTBI is asymptomatic, patients may not understand risk of developing active TB, LTBI therapy has potential side effects, and LTBI therapy is of long duration (usually 9 months) [10–12]. In a large prospective North American study, lower treatment completion rates were noted among females, US-born, Hispanic, and uninsured populations [13]. As a result, the proportion of persons who complete LTBI treatment in the USA ranges between 39 and 65%. These low adherence rates undermine the potential benefits of preventing TB progression in individuals with LTBI and maximizing TB control from a public health standpoint [14, 15]. Low adherence also increases the burden of active TB disease within the community and can increase the rate of drug-resistant TB strains.

One of the major shortcomings in TB control thus remains the difficulty in reaching marginalized populations for the purpose of TB prevention [16]. The ability to follow treatment plans in an optimal manner is frequently compromised by multiple barriers. Others have noted some of these barriers, including younger age, lower perceived risk for TB disease, and self-administered regimens [17]. Measures to improve adherence aim to (1) help patients address social issues which may hinder their ability to follow treatment, (2) enhance contact with health professionals, and (3) strengthen communication between health professionals and patients during treatment [18]. The best way to improve adherence to long-term treatment regimens may be through extended supervision of patients [19]. However, direct supervision of treatment is expensive and has mixed results in increasing LTBI treatment completion [20, 21]. Reminder trials for TB have demonstrated benefits on adherence to appointments [22]. Yet, treatment adherence and completion rates remain suboptimal across high-risk groups, and no intervention has shown consistent effectiveness [15]. For example, the role of education as a predictor of adherence has not been well-defined [15]. Similarly, the effect of immediate compared to deferred monetary incentives on adherence has not been shown to significantly differ [23].

### Potential benefits of text messaging

Over two trillion text messages were sent in the USA in 2011, with more than 80% of the US population owning a mobile phone and almost 70% of these phone owners regularly sending or receiving text messages [24]. Unlike the digital divide with online technologies, people of color and low-income individuals are more likely to text [25]. With this widespread adoption, texting offers promise for public health departments to make health information more readily accessible. Texting allows quick, direct communication that works on all types of mobile phones. Texting can be used in conjunction with other initiatives to establish and maintain contact between the patient and provider over the course of treatment. The information-motivation-behavioral skills model demonstrates that information is a prerequisite for good adherence, yet it is not sufficient in itself in explaining behavior [26]. Mobile phones can benefit both patients and providers by overcoming resource limitations, structural barriers, and behavioral limitations in providing motivation and the development of desired behavioral responses [27]. Conceptually, text messaging relies on constructs from the Social Cognitive Theory where positive outcome expectations, e.g., beliefs about the likelihood and value of the consequences of taking medication, as well as self-efficacy (beliefs about personal ability), substantially contribute to forming an intention to perform a desired action [28]. For example, participants in a multisite randomized clinical trial of HIV-infected adults initiating antiretroviral therapy asked to respond to a text message indicating that they had taken their medications were more likely to take their medications [29, 30]. Text messages have the advantage of being efficient and are considerably less invasive to daily lives compared to phone calls [31]. Mobility, instantaneous access, and direct communication are likely to enhance efficiency of service delivery [32, 33]. With increased efficiency, cost savings are substantial and include direct costs defrayed to the health system as well as opportunity costs of missed appointments and lengthy treatment duration [34, 35].

A stronger evidence base needs to be developed around the mobile health field for TB, before effective approaches can be implemented and high-quality data are lacking [36, 37]. Only recently have studies investigated the effectiveness of texting reminders for active tuberculosis treatment [34, 38, 39]. To our knowledge, no studies have been completed and only one study is currently being carried out in the context of latent TB infection [40]. As such, tailoring a reminder system for LTBI patients who self-administer medications could improve adherence to LTBI treatment and provide evidence for adopting or expanding reminder systems. A commonly used practice for LTBI is a phone call to remind patients to visit the clinic for a check-in and monthly refill. Since we would like to assess the independent effect of text messages on treatment adherence, we propose to evaluate the use of daily text messaging, in addition to the reminder phone call. We propose a study examining the feasibility of a randomized controlled trial using text messages to improve LTBI treatment adherence. This study will provide us the necessary data to design a large randomized controlled trial which will examine the effectiveness of text messaging.

### Study objectives

We aim to determine the feasibility and acceptability of text reminders for improving adherence in latent TB patients. Specific objectives of the current study are to (1) assess the feasibility of the intervention as indicated by participant recruitment and retention and (2) evaluate the acceptability of the intervention, as indicated by intervention adherence, outcome measurement rates, and feedback from participants.

Data will be used to design a definitive trial which will test the hypothesis that the intervention will improve medication adherence, as measured through an increase in treatment completion rates, and result in higher self-reported medication adherence, fewer missed appointments and doses, and a shorter course of treatment.

## Methods/design

### Overview

This is a single-blinded randomized controlled parallel trial to test the feasibility of using text messages to improve LTBI treatment adherence. Randomization will be performed with a 1:1 allocation. The project is funded through the American Lung Association and is being led by researchers at the University of Arizona with recruitment and collaboration taking place at the Pima County Health Department (PCHD) TB Control Program in Tucson, AZ, USA. This manuscript adheres to the SPIRIT checklist reporting guidelines (Additional file 1).

### Participants

Forty participants from PCHD are being recruited, with adequate representation expected from samples previously noted to fail treatment [13]. Pima County Health Department prioritizes LTBI screening based on recent contact to an infectious TB patient, migration from a high-burden TB country, as well as the USPSTF guidelines [9]. Persons who are at least 18 years of age and able to provide informed consent, agree to initiate LTBI treatment, are prescribed self-administered 4-month rifampin or 9-month isoniazid therapy, and have a phone that can receive text messages, will be eligible for the study. Participants will also need to be able to communicate via text messaging or have a family member or friend able to provide assistance with messages for the duration of the study. Patients are ineligible if they currently have active tuberculosis disease. Participants from the pilot will not be included in a proposed larger follow-up study.

### Participant recruitment and consent

All participants will be recruited directly from the PCHD Tuberculosis Control Program. A clinic nurse will refer interested participants to study personnel, at which point these personnel will assess eligibility and obtain informed consent. The referral will occur when a patient agrees to begin treatment for LTBI. Participants will be informed through the consent process that they may withdraw from the study at any time for any reason without it affecting their medical care. Participants will also be provided the purpose of the study, study objectives, as well as how study success will be measured [41]. The informed consent document will use simple language to minimize barriers posed by low literacy. A language line will also be used to verbally explain study materials, assist with language difficulties, and overcome reading difficulties. Family members or friends who are present at the time of recruitment will also be utilized for support and translation, but will not take the place of the language line.

Eligible individuals will be recruited over a 12-month period. Following consent, all participants will complete baseline assessments and will be randomly allocated to group.

### Randomization and allocation

Eligible patients who have given informed consent and completed baseline assessments will be randomly assigned to receive either text messaging and usual care or usual care only. A list allocating participants to the intervention or control arm will be generated by the biostatistician (MB), who has no patient contact, using the statistical software R. Randomized blocks of variable size will be used to ensure balance between the arms. Block size will be random to reduce predictability of the sequence. Each individual will be assigned a unique study code, which will be used throughout the research study in place of any identifying information. Participant identification and allocation will be placed in sealed opaque envelopes. Allocation codes will be concealed until study group is assigned. Participants will be identified to the research team only by phone number and study code.

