### Usual care

Standard of care for LTBI patients at this clinic includes an initial discussion of medication risks, benefits, and side effects. Treatment usually involves daily self-administration of medication for a prolonged period of therapy. Treatment typically involves taking rifampin 600 mg daily for 4 months or isoniazid 300 mg daily for 9 months. If a patient agrees to treatment, they are given a 30-day supply of medication. Subsequent follow-up involves monthly clinic visits, at which time there is an assessment of symptoms, side effects, and adherence; blood-work is performed; and another month’s supply of medication is provided. The usual practice of care with regard to adherence is a phone reminder prior to the next appointment.

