### Outcome measures

All outcomes will be assessed through in-person participant visits or collection from clinic records. Questionnaires will be completed by trained interviewers who are blinded to participant allocation.

The primary feasibility outcomes are summarized in Table 1.

**Table 1 Tab1:** Feasibility outcomes

Outcome	How assessed	Target
Recruitment	How many approached by clinic, how many referred, how many study eligible, how many consented; why ineligible or refused; how long to recruit each patient	40% recruitment rate, based on recruitment of all eligible
Retention	How many drop out at each monthly time point, who and why	70% retention rate
Patient satisfaction and acceptability	Patient perceptions, satisfaction, and acceptance of the intervention through pre- and post-surveys	75% satisfaction rate based on positive responses to questionnaires

While this pilot study will not have the power to detect differences in efficacy, efficacy outcomes will be measured to test procedures for early indication of a promising intervention. The primary efficacy outcome is the difference in proportion of participants completing treatment in each of the study groups. Successful treatment completion is defined as taking at least 80% of the doses of rifampin prescribed within 20 weeks [43]. Estimates of treatment completion will be used to indicate whether the treatment appears promising and to estimate sample size for a future definitive trial. Additional secondary outcomes include proportion of missed visits out of total scheduled visits; the number and length of delays in medication refill; number of missed doses; overall length of treatment (time to dropout); and self-reported adherence. While potentially overestimating true adherence, self-reported adherence is a robust measure of adherence [44, 45]. A brief pre-survey and more detailed semi-structured interviews will be conducted with all individuals to qualitatively assess preferences, attitudes, and satisfaction with the study, as well as barriers to adherence.

The following assessments will be completed by participants (Fig. 1), as per the SPIRIT Statement [46].

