### Statistical methods

Analyses regarding feasibility of the study will primarily be descriptive in terms of recruitment and retention rate, reasons for dropout, and deviations from protocol. Participation bias will be assessed by comparing individuals included in the study to study refusals as well as broader clinic participant characteristics.

Qualitative data will be transcribed and analyzed for patterns and themes using NVivo 10, a qualitative analysis program with which a member of the team has substantial experience [51, 52]. Answers to open-ended questions regarding barriers and benefits of the reminder systems will be categorized and described.

We will compare the proportion of participants completing treatment in each of the study groups in order to assess preliminary efficacy [43]. Results will be reported as the number (%) of participants for each treatment group, the risk difference, and 95% confidence intervals. Secondary outcomes will include proportion of missed visits out of total scheduled visits; the number and length of delays in medication refill; number of missed doses; overall length of treatment (time to dropout); and self-reported adherence.

Rescheduled or canceled appointments will not be considered as missed although rate of canceled or rescheduled appointments will be collected. Comparisons of the intervention group with the control group for all continuous or count outcomes will be carried out using *t* tests. Proportions will be compared using a non-continuity-corrected test of proportions. Time to dropout will be described using survival analysis methods.

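### Missed doses and refill delays are compared as raw counts although 4-month and 9-month courses are pooled, which costs precision (but not validity) on secondary outcomes

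*Protocol article*

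**What the plan says.** - Protocol article, Participants: eligible patients "are prescribed self-administered 4-month rifampin or 9-month isoniazid therapy". The regimen is therefore fixed and known before allocation. The same section gives the size: "Forty participants from PCHD are being recruited".
- Usual care: treatment is typically "rifampin 600 mg daily for 4 months or isoniazid 300 mg daily for 9 months", dispensed as 30-day supplies at monthly visits.
- Overview: "Randomization will be performed with a 1:1 allocation", so about 20 per arm.
- Randomization and allocation: "Randomized blocks of variable size will be used to ensure balance between the arms". No stratification factor is named.
- Statistical methods: "Comparisons of the intervention group with the control group for all continuous or count outcomes will be carried out using" t tests. The secondary outcomes listed there include missed doses and the number and length of refill delays, none of them scaled to the course prescribed. Missed visits, in the same list, are a proportion of scheduled visits. Time to dropout is to be described by survival methods.
- Outcome measures: "The primary efficacy outcome is the difference in proportion of participants completing treatment in each of the study groups", and "Successful treatment completion is defined as taking at least 80% of the doses of rifampin prescribed within 20 weeks". No counterpart is given for isoniazid.

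**The concern.** A patient who misses 10% of doses records 12 missed doses on the 4-month course and 27 on the 9-month course, with identical adherence. Refill delays behave the same way: 4 supplies against 9 give unequal numbers of chances to be late. A raw count therefore mixes adherence, which texting is meant to change, with course length, which it cannot change because the regimen is prescribed beforehand.

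Two costs follow. Course length adds variance to every between-arm comparison of these counts. With about 20 per arm, an unlucky split of regimens can also shift an observed difference for reasons unrelated to texting. The plan has the remedy in its own list, since missed visits are already scaled, and regimen is known for every participant.

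**Working it through.** The plan gives no figure for this point; its one precision statement concerns single proportions and plays no part here.

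**Inputs from the document.** N = 40, allocation 1:1, daily dosing, courses of 4 and 9 months. At 30 days a month that is 120 and 270 doses, a ratio of 9/4 = 2.25.

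**Inputs assumed, because the document does not give them.** Number on isoniazid: 12 to 20 of 40. Fraction of doses missed: 10–20%. Coefficient of variation (CV) of that fraction between patients: 0.6–1.0. Reduction from texting: 20–40%.

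**1. Chance imbalance.** With K isoniazid patients among 40 split 20/20, the number in one arm is hypergeometric(40, K, 20). This approximates unstratified blocks.

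| K | P(arms differ by ≥4 patients, 20 points) | P(≥6 patients, 30 points) |
|---|---|---|
| 12 | 30% | 8% |
| 20 | 34% | 11% |

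For other mixes the 20-point figure is 11% at K = 4 and 27% at K = 10 or 30.

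**2. What an imbalance does to missed doses.** Shift = imbalance × (270 − 120) × fraction missed. At 20 points this is 0.2 × 150 × 0.10 = 3 doses, or 0.2 × 150 × 0.20 = 6. With half on each regimen the mean course is 195 doses, so the shift is 0.2 × 150 / 195 = 15% of the mean count, whatever the fraction missed.

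**3. Variance added without any imbalance.** Take half on each regimen and the same distribution of missed fraction in both. Ignoring day-to-day binomial noise, the squared CV of the raw count is [75² + c² × (120² + 270²)/2] / 195², where c is the CV of the fraction and 75 is the SD of course length in doses.
- c = 0.6: (5,625 + 15,714) / 38,025 = 0.561, against 0.36 for the fraction, a ratio of 1.56.
- c = 1.0: (5,625 + 43,650) / 38,025 = 1.296, against 1.00, a ratio of 1.30.

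Keeping raw counts and adding regimen to a linear model recovers less: in simulation over several regimen mixes, the unadjusted variance was 1.1 to 1.3 times the adjusted one.

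**4. Power of the t test**, by simulation (20 per arm, half on each regimen, beta-distributed missed fraction, binomial doses):

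| Mean missed | CV | Reduction | Raw count | Fraction of doses |
|---|---|---|---|---|
| 20% | 0.6 | 40% | 51% | 69% |
| 20% | 1.0 | 40% | 23% | 29% |
| 20% | 0.6 | 20% | 14% | 19% |
| 20% | 1.0 | 20% | 8% | 10% |
| 10% | 0.6 | 40% | 49% | 65% |

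Repeat runs of the first row gave 49–51% and 67–69%. With no treatment effect, both analyses reject about 5% of the time.

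**5. Completion, as a separate matter.** Twenty weeks is 140 days, and 140/270 = 52% of a 9-month course. Reaching 80% takes 0.8 × 270 = 216 days, or 30.9 weeks. Read literally, the stated definition either does not cover isoniazid patients or cannot be met by them.

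**The case against.** The case on the other side is substantial, and much of it stands.

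- **Bias.** A reader might infer that pooling the regimens distorts the comparison. It does not. Unstratified randomisation is unbiased and the unadjusted tests hold their size.
- **Completion.** A reader might infer that the completion difference is materially affected too. The document gives 39–65% completion in the USA, not split by regimen, so any gap between regimens is an assumption. With assumed rates of 65% against 50% or 39%, the variance without adjustment is 0.98 to 1.05 times that with it, so adjustment gains almost nothing. The real difficulty is the rifampin-only definition, which stratifying would not cure.
- **Treatment length.** A reader might infer that it is tested without adjustment. The plan equates it with time to dropout and describes that by survival methods.
- **Sizing the next trial.** Only completion estimates are named for this. The Sample size section speaks generally of estimating variability in outcome measures but names no count outcome as a sizing input.
- **Stratification.** The sentence on blocks is true of arm sizes, and its silence on strata in a condensed article is not an error. The full protocol or SAP might add adjustment.
- **Purpose.** The pilot disclaims power for efficacy, and its primary outcomes are recruitment, retention and acceptability.

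What survives is narrow. The article does fix the test for count outcomes, fixes it as unadjusted, and lists missed doses and refill delays unscaled beside a visit outcome that is scaled. That is a stated choice, not a missing detail.

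**Conclusion.** The point holds as a minor one, confined to missed doses and refill delays. Analysing raw counts across courses that differ 2.25-fold gives away precision that is free to recover. With half on each regimen, the squared CV of missed doses is 1.3 to 1.56 times larger than it need be, and power in the first three scenarios rises from 14–51% to 19–69%. The gain nearly vanishes (8% to 10%) when high variability and a small effect coincide. An imbalance of 20 points or more, with a 30–34% chance if 12 to 20 of 40 take isoniazid, would shift mean missed doses by about 3 to 6.

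These sizes rest on assumed regimen mix, missed fraction, variability and effect. The direction does not: the count scales with the course by construction. If nearly all participants take one regimen, the point largely disappears. The primary feasibility outcomes are not touched.

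**What to change.** In Statistical methods:
1. Analyse missed doses as a proportion of doses prescribed, and refill delays per refill (month) due.
2. Adjust these comparisons for regimen, or report them by regimen.
3. Describe time to dropout separately by regimen.

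Stratifying any remaining allocations by regimen is optional.

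Separately, the completion definition under Outcome measures and the isoniazid eligibility under Participants must be reconciled before any regimen-stratified completion difference is reported. Which definition should apply is for the investigators to settle.

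The cost of the main change is a few lines of analysis wording. Regimen is known at entry and dose counts are already abstracted, so no new data are needed. The optional stratification would need a second set of envelopes.
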